## Abstract

**Background:**

Hypertension is the most prevalent chronic condition and is the leading cause of cardiovascular diseases, imposing enormous burdens on the healthcare system. Although telemedicine may provide improved blood pressure (BP) monitoring and control, it remains unclear whether it could replace face-to-face consultations for patients with optimal BP control. Thus, the primary objective of this study is to investigate whether participants assigned to the telemedicine group show non-inferior BP control compared to the usual care group at 12 months.

**Methods:**

This randomised controlled trial (RCT) will involve 364 patients receiving anti-HT medications who have well-controlled BP on out-of-office BP measurements, including HBPM or ambulatory blood pressure measurements (ABPM). Participants will be randomised to either the telemedicine (HealthCap) group or usual care (control) group (1:1). Patients in the intervention group will measure and transmit their 7-day home BP measurements (HBPM) to the physician’s office. The medications will be refilled without consultation when optimal control (<135/85 mmHg for patients without comorbidities and <130/80 mmHg for patients with comorbidities that increase cardiovascular risk) and safety questions are confirmed. Nevertheless, if any of the answers in the safety questions are positive or the HBPM mean is suboptimal, patients will have consultations as planned. Investigators will be blinded to the randomisation sequence and allocation. The primary outcome is the daytime ABPM systolic BP at 12 months. Secondary outcomes include HT treatment adherence, self-efficacy, number of visits to primary care clinics where they have clinical follow-up, health care utilisation other than general outpatient clinics (GOPCs) in both arms at baseline, 6 months, and 12 months. Acceptability will be assessed through interviews with the telemedicine study participants and the physician.

**Discussion and significance:**

This trial will examine whether patients in the telemedicine group would have non-inferior BP control compared to patients in the usual care group. It has the potential to change clinical practice and have important research implications because patients with optimal BP can monitor their BP through a telemedicine system and will have fewer frequent clinical visits. This will empower primary care and allow effective and safe allocation of scarce medical resources to patients in need. Moreover, it will save patients time because of the long wait to see doctors and collect medications in GOPCs. It is also encouraging the engagement of patients in their health because they will play a proactive role in managing their chronic illnesses.

**Trial registration:**

ClinicalTrials.gov NCT06524180. Registered on July 29, 2024. https://clinicaltrials.gov/study/NCT06524180?term=NCT06524180&rank=1#more-information.

**Supplementary Information:**

The online version contains supplementary material available at 10.1186/s13063-025-09350-3.

## Background

Hypertension (HT) is the most prevalent chronic condition (affecting approximately 30% of the world’s and Hong Kong’s [HK] adult population) and is the leading cause of cardiovascular diseases and death. Although approximately 50% of patients with HT in HK have optimal blood pressure (BP) control, these patients have doctors’ consultations every 16–18 weeks to monitor BP control and refill medications [1]. Owing to an ageing population and improved HT screening programme in HK, the number of HT patients requiring medical attention will increase and overload our primary care healthcare system. For instance, the recently established primary healthcare office will provide universal HT screening for all residents aged ≥45 years, while currently, approximately 50% of patients with HT are undiagnosed [2]. Therefore, a timely and novel strategy that can confirm good BP control and automatically refill medications in patients with good HT control is urgently needed to allocate healthcare resources better and empower HK primary care and patients.

Telemedicine is defined as the use of technology which allows the automatic exchange of medical information (i.e. BP readings) between patients and healthcare providers to manage diseases at a distance [3]. Since telemedicine allows confirmation of good home BP control without in-person consultations and drug refills, it has great potential to replace in-person doctor consultations and reallocates these resources to patients with more significant health needs [3]. In fact, telemedicine has improved patients’ BP in randomised controlled trials (RCTs) and can be cost-effective [4, 5]. A recent meta-analysis reported a 4 mmHg and 2 mmHg reduction in systolic BP (SBP) and diastolic BP (DBP), respectively, in patients receiving telemedicine. Telemedicine enhanced patients’ self-efficacy and treatment adherence by encouraging regular BP monitoring and self-management [6, 7].

However, the clinical role of telemedicine in patients with optimally controlled BP is unclear because existing RCTs included patients with elevated BP, and telemedicine typically represented more intensive treatments in these RCTs [3–7]. The ideal frequency of telemedicine monitoring in patients with optimal BP control remains unknown [3]. There is also uncertainty whether telemedicine can reduce or replace clinic visits, with limited relevant evidence [3]. Similarly, the cost and safety of telemedicine are under-reported in existing RCTs [3]. Importantly, the role and effectiveness of telemedicine are understudied in Chinese. With the latest meta-analysis on telemedicine and HT only including one Chinese RCT (*n* = 59), ranked as having a high risk of bias [6]. Understanding the factors to enhance the effectiveness and successful implementation of telemedicine systems, such as taking into consideration different cultures, patients’ age and education, and healthcare system organisations, is vital [8].

To examine the feasibility of using a telemedicine system to reduce doctor consultations, we conducted a 6-month pilot RCT (*n* = 49) in 2020 which randomised patients with optimal BP control to a telemedicine arm or a usual care arm [9]. The telemedicine system (called “HealthCap”) used in the pilot RCT was developed by our team. It can record home BP measurements (HBPM), provide automatic feedback on different BP levels, transfer BP data to the case physicians, and confirm optimal BP control on HBPM (details under methods) [9]. For patients randomised to the HealthCap intervention, drugs were prescribed in the clinic without doctor consultation, and the index physician’s consultation was deferred after optimal BP control was confirmed by HealthCap. Our pilot RCT found that (i) patients’ retention was high (98%), (ii) patients’ acceptability was high, which was further confirmed by patients’ interviews (interviewees reported that HealthCap was convenient, time-saving, cost-saving, and educational), (iii) no side effects or hospitalisation was detected in both groups, (iv) similar SBP/DBP control between the two groups at 6-month follow-up (systolic BP: 128.2 versus 126.9 mmHg [telemedicine versus usual care], *p* = 0.41), and (v) clinical visits were reduced in the telemedicine group (0.8 versus 2 consultations, *p* < 0.001) [9]. Our pilot RCT also confirmed the feasibility of using HealthCap in general outpatient clinic (GOPC) settings [9].

Despite the encouraging results from our pilot RCT, these results should be confirmed in an adequately powered RCT. Furthermore, a cost-minimisation analysis (i.e. cost saving from using HealthCap) should be performed if HealthCap is non-inferior to usual care. HealthCap can be cost-saving for healthcare systems (i.e. due to fewer consultations) and patients because it can reduce absence from work due to clinical visits and medication refills (which often take 3–4 h in GOPC). Moreover, telemedicine systems should also undergo formal validation prior to widespread implementation because they are considered medical devices, and medical societies recommend formal validation [3]. Finally, most existing telemedicine systems have not been validated, and a validated telemedicine system for HT is lacking in HK [10]. Validated HT apps/systems in Western countries are not available in Chinese, which is the only language most HK elderly can read and furthermore the health-related information may be irrelevant (e.g. not tailored to locally available clinics or medical resources).

## Aims and objectives

The aim of the study is to investigate if a telemedicine system can replace doctor consultations to achieve non-inferior blood pressure in patients with controlled hypertension. The primary objective is to evaluate whether patients assigned to the telemedicine (HealthCap) group demonstrate non-inferior BP control compared to patients in the usual care group at 12 months. Secondary objectives include (i) assessing patients’ adherence, self-efficacy, number of primary care clinic visits, and healthcare utilisation in both arms; (ii) assessing acceptability to physicians and patients in the telemedicine group; and (iii) conducting a cost-minimisation analysis if HealthCap is non-inferior.

## Methods

### Trial design and patient involvement

This protocol was written with reference to the Standard Protocol Items: Recommendations for Interventional Trials (SPIRIT) [11]. The SPIRIT checklist can be found in additional document 1. This is a parallel-arm RCT in which 364 patients with optimally controlled HT will be randomised in a 1:1 ratio to the HealthCap telemedicine (intervention) and usual care (control) groups and followed up for 12 months. For the primary outcome, we hypothesised that patients randomised to the telemedicine (HealthCap) group would have non-inferior BP control compared to patients allocated to the usual care group at 12 months. The RCT was pre-registered on clinicaltrials.gov (NCT06524180) and was approved by the Joint Chinese University of Hong Kong-New Territories East Cluster Clinical Research Ethics Committee (2023.525) and The University of Hong Kong/Hospital Authority Hong Kong West Institutional Review Board (UW25-086). The study complies with the Declaration of Helsinki.

Conducted during the peak of the COVID-19 outbreak in HK, the recruitment rate of the pilot trial was suboptimal for a main RCT (8 participants/month by 2 recruiting doctors) [9]. Thus, necessary modifications were made to ensure adequate recruitment in this trial.

### Trial setting

Patients will be actively recruited by doctors, nurses, research assistant(s), and posters in GOPCs at New Territories East cluster and Hong Kong West cluster in Hong Kong. The detailed list of participating recruitment sites can be found in additional document 2.

### Recruitment and participant timeline

Our recruitment methods include in-person visits to recruitment sites, written materials (such as posters and leaflets), and referrals. Healthcare providers will identify potential patients during their follow-ups on hypertension and introduce the programme. All hypertension patients will receive periodic assessments under the Risk Assessment and Management Programme for Hypertension (RAMP-HT), during which the research team will directly approach them to discuss the project. Patients who see the posters and express interest in the trial can also register using the QR code provided in the poster or contact the research assistants directly through the communication tool (i.e. WhatsApp). Any issues with the registration process will be promptly addressed by our research team.

Interested patients will be contacted by the research team and undergo an eligibility screening. To standardise our recruitment approach, we conduct staffing training and hold meetings with healthcare providers in the GOPCs involved before patient enrolment. We also continuously engage doctors in each recruiting GOPC to encourage referrals of patients with well-controlled hypertension. Once patients are deemed eligible, they will be asked to sign informed consent online. Furthermore, the research team has developed strategies to ensure adequate enrolment and achieve the target sample size, including monitoring recruitment rates monthly and addressing challenges through regular meetings with healthcare providers. Patients will then be invited to the data collection session, during which all baseline measures will be assessed, patients will be randomly assigned either to the experimental group or the control group (T_0_, baseline). Afterwards, patients will be assessed at baseline (T_0_), 24 weeks (T1), and 1 year (T2) (Table 1).

**Table 1 Tab1:**
[figure not shown]
Schedule of enrolment, interventions, and assessments

*ABPM* ambulatory blood pressure monitoring, *BP* blood pressure, *HbA1c* glycosylated haemoglobin, *ACR* albumin-to-creatinine ratio

### Eligibility criteria

Patients who meet *all* these criteria will be included: (i) having a diagnosis of essential HT; (ii) on anti-HT medications; (iii) well-controlled HT on out-of-office BP measurements, including HBPM or ambulatory blood pressure measurements (ABPM) (measurement algorithm and details under methods) [12]. ABPM or HBPM are preferred to office BP due to their superior reproducibility and predictivity to cardiovascular outcomes [13, 14]. Furthermore, office BP misclassifies 30–40% of patients as having suboptimal BP control due to white-coat effect [15]. From our pilot study, some patients with optimal BP are reluctant to undergo ABPM before recruitment into the RCT, and HBPM is more acceptable to these patients and is therefore included. According to local and international guidelines, optimal out-of-office daytime BP should be <135/85 mmHg for patients without comorbidities and <130/85 mmHg for patients with comorbidities that increase cardiovascular risk (i.e. stroke, ischaemic heart diseases, heart failure, diabetes mellitus (DM), and chronic kidney diseases) respectively [12, 16]; (iv) can read basic Chinese (language used in the HealthCap); (v) have used any mobile app (not HT-related) in the previous 1 year; and (vii) aged between 18 and 80.

Patients will be excluded if any of the following criteria are met: (i) cannot provide informed consent; (ii) unwillingness to conduct HBPM or repeated ABPM; (iii) relative contraindications to ABPM (i.e. diagnosed atrial fibrillation, nighttime workers, occupational drivers, or patients with bleeding tendencies); (iv) have severe mental illnesses that impair their ability to use HealthCap, including those diagnosed with schizophrenia, dementia, or as being actively suicidal; (v) a diagnosis of other acute or chronic diseases that need regular physical assessments and/or medication changes (e.g. suboptimally controlled DM [e.g. glycosylated haemoglobin (HbA1c) ≥ 7%], depression requiring medications, active cancer); and (vi) predicted lifespan of <1 year.

All GOPCs within the New Territories East cluster and Hong Kong West cluster in Hong Kong are the eligible recruitment sites. Regarding the delivery of intervention, only the research team members who have been trained are eligible. All members in the research team have been trained on the study’s objectives and patient eligibility criteria, as well as to provide patients with instruction on how to use the HealthCap correctly. The physicians in charge have also been trained to utilise the HealthCap for monitoring patients’ blood pressure control and reviewing questionnaire responses before each patient’s visit. While patients are recruited by doctors, nurses, and the research team (including investigators and research assistants) during their visits to the clinics for hypertension care, eligibility will be further confirmed by the research assistants when patients are referred to the trial.

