### Randomisation/blinding

Stratified randomisation with blocks of four or six will be used according to (i) the presence or absence of diseases that increased cardiovascular risk and required a lower BP target (<130/80 mmHg) (including DM, history of cardiovascular diseases, history of chronic kidney disease) and (ii) the number of anti-HT medications (<3 or ≥3) because the number of medications affects medication adherence and the likelihood of maintaining optimal BP control [17]. The randomisation sequence will be generated by an independent statistician, using the statistic programme Random Allocation Software, version 1.1.0, printed out, and sealed in light-opaque envelopes, which will only be opened by the research assistant after a participant’s eligibility is confirmed and the consent form is signed. Due to the nature of the intervention, blinding the investigators, participants, and healthcare providers will be infeasible after randomisation. However, the independent statisticians who will conduct the analysis will remain blinded.

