### Intervention/control arm

#### Intervention arm: telemedicine

Patients will be: (i) given a validated HBPM device (ORMON HEM-7120) with appropriate cuff size, (ii) taught the HBPM technique, and (iii) taught to record HBPM readings using the HealthCap mobile app on their smartphones.

Participants randomised to intervention will be reminded to take dual BP readings in the morning and evening for 1–2 weeks before the index consultation. These BP readings will be automatically sent to a computer at the clinic. When the HBPM mean is optimal (i.e. <135/85 mmHg or <130/80 mmHg [for patients with cardiovascular diseases, renal diseases, and DM]), other parameters will be checked using an online questionnaire, and responses will be screened by the physicians, including (i) self-reported good drug compliance and no drug side effects, (ii) absence of symptoms of complications (i.e. chest pain and hemiplegia), (iii) absence of hyperglycaemia and hypoglycaemia symptoms (only for patients with DM), and (iv) no other health complaints that need consultation. When all the answers are negative, medications will be delivered to the patient by tracked mail, and the index physician appointment will be deferred for 16–18 weeks (the usual follow-up period for these patients is now 16–18 weeks). The index consultation will proceed as scheduled if BP is suboptimal or any of the safety questions screen is positive. HealthCap has an automatic feedback function. For example, if BP is dangerously high (i.e. SBP ≥ 180 or DBP ≥ 110 mmHg), HealthCap will recommend a recheck and advise attendance at the emergency department if BP remains elevated (Fig. 1).

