### Criteria for discontinuing or modifying allocation

Participants are encouraged to adhere to their assigned allocation as closely as possible. If any of the answers to the safety questionnaire are positive or the mean BP value from 7-day HBPM is suboptimal, the patient in the intervention group will receive usual doctor consultation. This consultation is part of the intervention and does not constitute a modification of allocation. Although there are no criteria for allocation modification, participants may withdraw from the study at any time if they choose to.

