### Statistical analysis

The baseline characteristics of the participants in the two arms will be described using means with SD and proportions for continuous and categorical variables, respectively. The effect of the HealthCap telemedicine system on SBP measured by ABPM (our primary outcome) will be examined using analysis of covariance (ANCOVA) with baseline SBP measured by ABPM and the treatment group as the covariate, following the intention-to-treat (ITT) principle, that is, patients will be encouraged to conduct ABPM at 12 months regardless of whether they comply with the assigned intervention. A per-protocol (PP) analysis will be conducted for sensitivity analysis. PP analysis provides some protection for theoretical increases in the risk of type I errors (erroneously concluding non-inferiority). Our modified ITT (mITT) data comprised all patients according to and were included in the random allocation of complete data. We defined the PP population as participants who met the mITT definition but did not receive intervention treatments. Based on a previous meta-analysis, we set the non-inferiority margin for ABPM SBP at 2 mmHg [26]. We accepted the non-inferiority of telemedicine over usual care (in a 0.0125-level test after Bonferroni correction for multiple testing) if the lower bound of the two-sided 95% confidence interval (CI) (equivalent to the upper bound of the one-sided 97.5% CI) was within the non-inferiority margin. Subgroup analysis will be conducted in cases of unbalanced baseline characteristics and for patients with and without indications of a lower BP target (i.e. <130/80 mmHg). Additionally, missing data will be addressed through multiple imputation.

Qualitative data will be analysed by at least 2 investigators using inductive thematic analysis as described by Braun and Clarke [28]. Therefore, digital recordings will be transcribed verbatim. The recordings will be listened to several times, and the transcripts will be read and re-read by at least 2 investigators. After familiarisation, codes and then themes will be generalised. The investigator team will discuss the themes to determine and decide on any over-arching themes. The Consolidated criteria for Reporting Qualitative Research (COREQ) Checklist will be followed throughout the qualitative research part to ensure comprehensiveness and transparency in reporting qualitative findings [29].

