## Trial status

This trial is actively recruiting participants (114/365). This trial is ongoing and has a planned duration of 36 months. The recruitment began on 1 October 2024, and the estimated date of recruitment completion is 31 May 2026. The current protocol is version 2. If any changes needed to be made to the protocol, the relevant part of the study, as well as the record in the trial registry, will be updated (ClinicalTrials.gov, NCT06524180).

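### The entry BP limit for patients with comorbidities (<130/85 mmHg) is looser than the refill limit (<130/80 mmHg), so a diastolic of 80–84 counts as controlled at entry but suboptimal for refill

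*Protocol article*

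**What the plan says.** All references are to the Protocol article.

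- **Eligibility criteria, inclusion (iii).** The limit is "<130/85 mmHg for patients with comorbidities that increase cardiovascular risk". The group listed is stroke, ischaemic heart disease, heart failure, diabetes and chronic kidney disease. For everyone else, "optimal out-of-office daytime BP should be <135/85 mmHg for patients without comorbidities".
- **Intervention arm: telemedicine (refill rule).** Drugs are refilled without a consultation when the home BP mean is below 135/85 mmHg, or "<130/80 mmHg [for patients with cardiovascular diseases, renal diseases, and DM". If the mean is suboptimal, the index consultation goes ahead.
- **Abstract, Methods.** The refill rule is restated as "<130/80 mmHg for patients with comorbidities that increase cardiovascular risk".
- **Randomisation/blinding.** One stratification factor is the presence of diseases that "required a lower BP target (<130/80 mmHg".
- **Statistical analysis.** A subgroup analysis is planned "for patients with and without indications of a lower BP target (i.e. <130/80 mmHg".
- **Criteria for discontinuing or modifying allocation.** On a HealthCap patient seen because BP is suboptimal: "This consultation is part of the intervention and does not constitute a modification of allocation".

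**The concern.** The trial asks whether telemedicine can replace consultations in patients whose BP is controlled. That requires the definition of controlled at entry to match the one that releases a refill. For patients without comorbidities it does. For patients with comorbidities the diastolic limits differ by 5 mmHg, in the one place where the figure decides who is enrolled.

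A HealthCap patient who enters in the gap and stays there keeps the usual consultations. Such patients say little about replacement and reduce the visits saved, which feeds a secondary outcome and the cost analysis. They also make care in the two arms more alike. In a non-inferiority trial that pulls any true harm towards zero and so favours the non-inferiority conclusion.

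**Working it through.** **Step 1. Is it the same group of patients?** The disease lists under Eligibility criteria, Randomisation/blinding and Intervention arm describe essentially the same patients: cardiovascular disease, kidney disease and diabetes. The abstract and the eligibility criterion use the same descriptive phrase with different figures. The limits therefore apply to one group.

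**Step 2. Limits side by side.**

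| Place | Without comorbidities | With comorbidities | Role |
|---|---|---|---|
| Eligibility criteria (iii) | <135/85 | <130/85 | decides entry |
| Intervention arm | <135/85 | <130/80 | decides refill |
| Abstract | <135/85 | <130/80 | restates refill |
| Randomisation/blinding | – | <130/80 | labels a stratum |
| Statistical analysis | – | <130/80 | labels a subgroup |

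The operating conflict is between the first two rows, and only in the diastolic part. Strata and subgroups are defined by presence of disease, so no patient's membership changes.

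**Step 3. Which readings fall in the gap?** Entry requires SBP <130 and DBP <85. Refill requires SBP <130 and DBP <80. At SBP 125, the whole-number diastolic values that pass entry and fail refill are 80, 81, 82, 83 and 84 mmHg. With entry set to <130/80, none remain.

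**Step 4. Scale.** The article gives neither a diastolic distribution nor a comorbidity prevalence, so the number affected, k, has to be assumed.

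- Arm size: 364/2 = 182.
- Refill checks in 12 months at 16–18-week intervals: 52/18 = 2.89 to 52/16 = 3.25.
- Index visits in the arm: 182 × 52/18 = 526 to 182 × 52/16 = 592.
- Visits not replaced if all k fail every check: k × 2.89 to k × 3.25.
- Dilution of a true 2 mmHg difference if those k show no difference from usual care: 2 × k/182.

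| Assumed k | Share of arm | Visits not replaced | Dilution (mmHg) |
|---|---|---|---|
| 5 | 2.7% | 14–16 | 0.05 |
| 10 | 5.5% | 29–33 | 0.11 |
| 20 | 11.0% | 58–65 | 0.22 |

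Each row is an upper bound for its k. BP is rechecked every cycle, so some patients will pass later checks. Entry may also be by ambulatory measurement while refill uses home readings, so a diastolic of 80–84 at entry does not guarantee a failed check.

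**Step 5. How much enrolment remains?** Trial status reports "This trial is actively recruiting participants (114/365". Against the target of 364, 364 − 114 = 250 were still to be enrolled, and 250/364 = 69%. This is the position when the article was written.

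**The case against.** The strongest reply is that this is a slip with little consequence. One place stands against four, no reason is given for a looser diastolic limit, and the same inclusion list has a numbering gap from (v) to (vii). Only entry and refill conflict in operation; the other mentions restate the refill rule or label a disease group. Nothing shows that 130/85 was used at screening. A consultation for suboptimal BP belongs to the intervention, so an affected patient is still managed as specified and analysed by intention to treat. The planned lower-target subgroup already contains every affected patient.

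Much of this stands. A slip is the likelier explanation, the effect on the primary comparison is small, and the figures per 10 patients give scale only and do not estimate how many are affected. Because entry and refill may rest on different measurement methods, a flag on the entry diastolic would also identify refill failures imperfectly.

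It does not remove the point. The odd figure sits in the eligibility rule, and under Eligibility criteria the staff are trained on those criteria and research assistants confirm eligibility. The written number may therefore be the one applied. The planned subgroup pools affected patients with all others who have comorbidities, so it would not show their influence.

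**Conclusion.** The concern holds. The article gives two different limits for the same patients and reconciles them nowhere. A diastolic of 80–84 mmHg with systolic below 130 is controlled for entry and suboptimal for refill.

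The consequence is modest. There is no safety gap, and the sample size, strata and subgroups are untouched. The likely cost is a smaller saving in visits and some blurring of the question about replacement. Any effect on the primary BP comparison is small, in the direction of non-inferiority, and arises only if 130/85 was actually applied at screening. The document does not say whether it was, or how many patients are affected. The mismatch itself is certain; its effect on the trial is not. It should be corrected while recruitment is open.

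**What to change.** 1. Ask the sites which diastolic limit they apply when screening patients with comorbidities.
2. If 130/80 is intended, change inclusion criterion (iii) to <130/80 mmHg, matching the refill rule. If a looser entry limit is intended, state it and justify it in one sentence.
3. Only if 130/85 was used at screening, flag participants with comorbidities and a qualifying diastolic of 80–84 mmHg in both arms, recording whether it came from home or ambulatory measurement. Add a sensitivity analysis of the primary outcome and the visit count without them.

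The cost is one query and a one-figure correction or one added sentence. Under the article's own amendment plan, a change to eligibility goes to the ethics bodies for approval first. Recruitment could slow slightly if sites have been using 130/85.
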